## Abstract

**Background:**

Intimate partner violence (IPV) can result in significant harm to women and families and is especially prevalent when women are pregnant or recent mothers. Maternal and child health nurses (MCHN) in Victoria, Australia are community-based nurse/midwives who see over 95% of all mothers with newborns. MCHN are in an ideal position to identify and support women experiencing IPV, or refer them to specialist family violence services. Evidence for IPV screening in primary health care is inconclusive to date. The Victorian government recently required nurses to screen all mothers when babies are four weeks old, offering an opportunity to examine the effectiveness of MCHN IPV screening practices. This protocol describes the development and design of MOVE, a study to examine IPV screening effectiveness and the sustainability of screening practice.

**Methods/design:**

MOVE is a cluster randomised trial of a good practice model of MCHN IPV screening involving eight maternal and child health nurse teams in Melbourne, Victoria. Normalisation Process Theory (NPT) was incorporated into the design, implementation and evaluation of the MOVE trial to enhance and evaluate sustainability. Using NPT, the development stage combined participatory action research with intervention nurse teams and a systematic review of nurse IPV studies to develop an intervention model incorporating consensus guidelines, clinical pathway and strategies for individual nurses, their teams and family violence services. Following twelve months’ implementation, primary outcomes assessed include IPV inquiry, IPV disclosure by women and referral using data from MCHN routine data collection and a survey to all women giving birth in the previous eight months. IPV will be measured using the Composite Abuse Scale. Process and impact evaluation data (online surveys and key stakeholders interviews) will highlight NPT concepts to enhance sustainability of IPV identification and referral. Data will be collected again in two years.

**Discussion:**

MOVE will be the first randomised trial to determine IPV screening effectiveness in a community based nurse setting and the first to examine sustainability of an IPV screening intervention. It will further inform the debate about the effectiveness of IPV screening and describe IPV prevalence in a community based post-partum and early infant population.

**Trial registration:**

ACTRN12609000424202

## Background

Intimate partner violence (IPV) has been defined as any behaviour by an intimate partner which causes physical, sexual or psychological harm and IPV results in lasting health damage particularly for women and children [1]. Pregnant women and those with infants are especially vulnerable to IPV [2,3]. During pregnancy, IPV has been estimated at between four to eight percent. It can commence, continue or escalate in pregnancy and continue into the postpartum period [4] with serious physical and emotional consequences [5,6].

This study is located in Melbourne Australia, where IPV among women in the childbearing years is estimated to be the major contributor to the burden of illness (especially to mental health issues) amongst women of childbearing age. It is also a significant cause of adverse pregnancy outcomes [7-9]. IPV has a significant impact on women's parenting abilities, ultimately compromising their children's development [9]. Current research indicates that many children witnessing IPV can experience behavioural, emotional, developmental and psychobiological problems and difficulties with social competence in the longer term [10]. The damage can be incremental, but is also cumulative and while some children demonstrate resiliency, it is not yet clear why. Therapeutic services for mothers and their children who have experienced violence are now developing and offer valuable sources of referral if the problem is detected early and referrals made.

The potential for health services to support women and children experiencing IPV in the early infant years has been recognised with increasing government policies around screening for IPV in the perinatal periods [11]. However, the evidence of benefit for women and children of screening for IPV is scarce [12-14]. Nevertheless, in spite of this lack of evidence, screening all women is a common policy initiative and primary health care professionals are increasingly mandated to screen for IPV, especially in the childbearing years.

Health care professionals are commonly reluctant to ask about IPV and women may also be reluctant to disclose. Common barriers for health-care professionals’ inquiry have been found to be lack of professional training, support, resources and workload [15]. While there is evidence that training can increase clinician confidence, rates of identification and referral in a given study period, a major problem is the lack of evidence of the sustainability of health-care provider behaviour change and evidence for subsequent effective interventions [14]. This paper reports the protocol for an IPV screening randomised trial located in maternal and child health nurse clinics in Melbourne, Australia with an evaluation of the elements contributing to sustained screening practice.

### Screening for intimate partner violence (IPV)

IPV screening in health care systems can be defined as routine and systematic inquiry of all presenting women about their experience of intimate partner violence, using a consistent set of questions [16]. It remains a controversial subject as reviewers of the same evidence have come to different conclusions about its effectiveness, and as to whether it should be recommended [14,16-18]. Scholars have identified many barriers to universal IPV screening, including health care provider attitudes, heavy workloads, and lack of recurrent training, of adequate referral services and other resourcing support, and the presence of partners during consultations [14,19-22]. Nevertheless, governments are increasingly turning to universal screening as a policy option with varying levels of readiness to address the identified barriers to sustaining screening practices. There have been varying rates of screening coverage reported, depending on whether screening data are collected routinely or ‘snapshots’ are taken when service providers know their governments are scrutinizing performance at a particular time [16]. While routine screening is commonly assumed to be a desirable goal, a recent trial of an alternative approach, system supported ‘case finding’ or inquiry when IPV symptoms are present by primary care providers, was successful in raising identification and referral numbers, although benefits for women are unknown [23].

### The Victorian maternal and child health service and the context for IPCV screening

Victorian maternal and child health nurses (MCHNs) are trained nurse midwives who visit over 95% of all Victorian mothers with newborns at home and continue to offer support at their local centres until the children are six years old [24]. This free, universal, comprehensive primary health-care service aims to provide health promotion, illness prevention, early detection of developmental problems, and intervention to enhance the health and wellbeing of young children and their families. Australia has three tiers of government: federal or national; state (or territory) and local government or council. MCHN nursing is located and managed in the complex local government environment, while implementing policies formulated at state government level. They are often funded at local government level (usually 60% local government and 40% state government).

In late 2009, just as this proposed trial of IPV screening versus usual care was funded, a new comprehensive approach to screening children and their mothers for other common problems and developmental delays, Key Ages and Stages (KAS), was introduced into Victorian maternal and child health nursing practice [25]. Under the new Key Ages and Stages protocol, MCHNs are now required to screen all mothers for family violence - the government’s preferred term, which includes child abuse (not only IPV) - when their babies are four weeks old. MCHNs were provided with three hours training to use a Common Risk Assessment Framework, offering a common definition of IPV for health care providers, police, family violence services and courts, symptoms to look for and referral processes. Included in KAS strategies were computer prompts for the now mandated four week IPV screening, any screening at a later consultation, and the requirement to report regular data about IPV screening, safety plans and referrals and other child health screening and referral rates to government.

Nurses are required to ask the following questions about family violence:

1. Are you in any way worried about the safety of yourself or your children?

2. Are you afraid of someone in your family?

3. Has anyone in your household ever pushed, hit, kicked, punched or otherwise hurt you?

4. Would you like help with this now?

### MOSAIC (MOtherS' advocates in the community)

Prior to this government initiative, in our previous IPV trial of non-professional mother-to-mother support for pregnant or recent abused mothers, known as MOSAIC [26], MCH nurses struggled to identify and refer clients experiencing violence despite comprehensive six-hour training by a domestic violence training agency and additional resources (referral booklets, posters etc.). An impact evaluation conducted at the end of the study, showed that 66% of nurses said that they were comfortable or very comfortable asking about partner violence, while 18% remained uncomfortable. Thirty-five percent cited partners or family members being present as the major obstacle to asking about IPV, followed by fear of embarrassing women (14%) and the need to focus on the child as their priority (13%). When asked what made it difficult, 42% of nurses said women's reluctance to take further steps, referral agencies’ waiting lists (22%) and the difficulty of finding support for women with special needs (17%). When asked what should be put in place to assist other nurses to develop their skills and increase their confidence in this area, nurses suggested regular training (1); MCHN specific clinical guidelines for IPV (2); and an MCHN clinical pathway (3).

Following on from MCHN feedback in MOSAIC, this study originally aimed to compare implementation of IPV screening with usual care; however with the introduction of mandatory IPV screening of all recent mothers when babies are four weeks old, the trial design was modified to evaluate an enhanced model of IPV screening addressing some of the identified challenges for nurses and addressing the issue of sustainability, compared with basic mandatory IPV screening.

### Trial registration

This trial was registered with the Australian and New Zealand Clinical Trials Registry (ACTRN12609000424202).

### Ethics

This study was approved by the Human Ethics Committee, La Trobe University (UHEC 08–142) and also by the University of Melbourne and the Victorian Government Department of Education and Early Childhood Development.

### Aims

1) To compare whether, after implementing an evidence-based consensus model of good IPV practice for twelve months, MCH nurses in the intervention arm more frequently than nurses in the comparison arm

• Ask about IPV among their client population

• Refer women experiencing IPV to services

• Inquire about the safety of women and children in the relationship

2) More women attending MCH centres in the intervention arm than in the comparison arm:

• Are asked about IPV

• Disclose/discuss any abuse and

• Are satisfied with the quality of care and support they receive

3) To provide an accurate estimate of the proportion of MCH clients who have ever or who are currently experiencing IPV and those abused when pregnant

### The primary outcomes for the study are to

1. Increase the proportion of women (15%) reporting that they have been asked about family violence or nurses reporting they have screened for family violence (i.e. questions from the Key Ages and Stages protocol)

2. Increase the proportion of women disclosing IPV (discussing IPV with MCH nurse) or nurses reporting discussing safety plans

3. Increase the proportion of referrals reported by nurses or women reporting being offered referrals

### Secondary outcomes are to

1. Estimate the prevalence of any IPV in the previous 12 months (measured with the Composite Abuse Scale, ≥3-6, and ≥7), IPV during pregnancy and any reported child abuse

2. Increase the proportion of MCH clients reporting satisfaction with quality of care and support they receive for themselves, their partners and their children

3. Investigate the proportions of women reporting any harm arising from (a) responding to questions about IPV in their MCHN consultation or (b) responding to questions about IPV in the survey)

### Design

MOVE is a cluster randomised trial. It is located in MCHN teams in the north-west suburbs of Melbourne, consisting of 80 nursing centres and over 160 nurses (Figure 1).

**Figure 1 F1:**
[figure not shown]
MOVE processes.

#### Recruitment of clusters: MCH nurse teams in north west Melbourne

Team leaders of eight MCH teams, located in eight local government areas were invited to participate in a previous study MOSAIC [26] and all agreed. Each team leader and their manager signed a supplementary letter to the original Memorandum of Understanding to participate in this subsequent study.

#### Randomization

The randomization of nurse teams at that time occurred at a public randomization meeting. Names of the MCHN teams, stratified by numbers of births per local government area and paired in size, were concealed in opaque envelopes and the random selection made by an invited guest from outside the project or research team. MCH Team Leaders were present to ensure the fairness of the process and to check the contents of the envelopes prior to their being sealed. For MOVE, all eight teams agreed to the reverse of the previous randomisation allocation, so that teams allocated to comparison status in MOSAIC formed the intervention arm for MOVE and those previously allocated intervention status formed the comparison arm.

#### Blinding (allocation concealment)

Given the nature of the intervention, it has not been possible to blind MCHN teams or nurses to their status. The Project Coordinator is not blind to MCHN team participant status either, as she is required to liaise with intervention team MCHN consultants. Women attending the MCHN service are blind to their status as randomization is by cluster and consent to participate in the trial was given at MCH team level.

#### Blinding (outcome assessment)

All outcome and process evaluation data are self-completed by women and nurses and are anonymous:

(a) MCHN staff complete process and impact survey instruments on line using an anonymised format and data are stored in a secure database

(b) MCHN complete anonymised routine computerized screen data that are summarized annually and forwarded to the Department of Education and Early Childhood Development

(c) Names and addresses of women attending MCH clinics are not accessible to research staff because of privacy regulations. Surveys are sent to women in anonymised questionnaire booklets mailed to their home by a local government agency with an accompanying letter from their MCHN team leader. Outcomes were pre-specified at the time of our trial registration. Analyses are to be carried out by the study statistician blinded for trial arm following data entry of women’s survey responses by an independent data company.

#### Survey sample size calculation

(b) We calculated that around 8-10% of women attending each of the eight MCH services will have been abused in the previous 12 months [4]. Following twelve months implementation, we will send a mailed questionnaire to all women who have given birth in the previous 8 months in both the comparison and intervention municipalities (5000 per arm). This sample size enables us to detect a predicted increase of 15% average disclosure found previously in a screening intervention of screening vs usual care [27]. We have taken into account both the numbers of births in participating local government areas (using most recent published data (2005), the likely response fraction (55-65% following mailed surveys and a reminder postcard - a modified Dillman procedure) and also adjusted for clustering. We adjusted for an intra-cluster correlation of 0.02 from a previous IPV primary care study [28].

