#### Checklists

These data will only be available in the intervention arm, as they are a screening intervention tool (see below). Nurses use these screening self-completion forms with women and retain these for collection by MOVE research staff. They also record the screening consultation time (three or four months or later) and these will be analysed especially for the three month screening point, when routine data are not recorded.

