### Screening time

#### The move intervention model

MCH nurses expressed concern about an early screening time (e.g. home visit or four weeks) for the following reasons: (a) women were still recovering from the birth and focused their attention on the baby’s not their own needs; (b) nurses had had insufficient time to establish a trusting relationship with the woman which would make it easier to ask a sensitive question and enable disclosure (c) >30% of Victorian women have had Caesarean section and advised not to drive for six weeks, so are frequently accompanied by someone, making it sometimes challenging to ensure screening safely. Nurses therefore suggested that the optimum screening time would be at a three or four month visit when women could be advised ahead of time that the visit would be focused on their needs and that they would be completing a women’s health checklist. They also suggested that they could ask women not to bring other children if possible; and told accompanying partners that the questions would include discussion of menstruation and breast problems, and that partners may not want to be present. Two teams created an additional woman-focused three month visit, and the other two teams added fifteen minutes to the four month KAS-funded visit to be focused on maternal needs.

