### Implementation

Following all stakeholders’ agreement with the new model, nursing consultants and MOVE staff briefed the intervention teams and provided them all with newly developed resources (http://www.latrobe.edu.au/mchr/html/move.html) including a guide to IPV documentation. Teams undertook to implement the MOVE model over a twelve month period. During the intervention period, MOVE research staff remained at a distance to enhance sustainability, and reliance on research staff was kept to a minimum.

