##### Women’s survey questionnaire

We have developed a questionnaire survey to be sent to 10,000 women (5000 in either arm) who have given birth over an eight month period. This sample gives us power to detect differences in the primary outcome. Included are all the primary and secondary outcome measures and a valid and reliable measure of intimate partner violence (Composite Abuse Scale) [29].

The data management company employed to manage the survey data has been subcontracted to the local government councils who have given the company staff access to women client’s addresses. They will mail the surveys and two rounds of reminder cards. Surveys will be returned to the company for electronic data entry and double-coding.

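### The women's survey covers births in the 8 months before mailing, but MOVE's checklist visit comes at 3 or 4 months, so up to about 44% of intervention-arm women may not yet have reached it

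*Protocol article*

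**What the plan says.** Three parts of the Protocol article bear on this.

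- **Who is surveyed, and when.** Survey sample size calculation: "Following twelve months implementation, we will send a mailed questionnaire". The same sentence defines the recipients: "a mailed questionnaire to all women who have given birth in the previous 8 months". Women's survey questionnaire gives the size as "10,000 women (5000 in either arm) who have given birth over an eight month period". Neither section sets a lower limit on the baby's age.
- **When MOVE screening happens.** The move intervention model: "Two teams created an additional woman-focused three month visit, and the other two teams added fifteen minutes to the four month KAS-funded visit". The Checklists section agrees: "They also record the screening consultation time (three or four months or later". Under Implementation, "Teams undertook to implement the MOVE model over a twelve month period".
- **What the survey feeds.** The primary outcomes list lets women's reports supply all three outcomes: being asked, discussing abuse, and being offered referral. The survey section says the questionnaire contains every primary outcome measure.

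Mandatory screening at four weeks applies to mothers in both arms. Nurse routine data are a second source for the primary outcomes, compared at four weeks, four months and twelve months. Neither the sample size text nor the analysis section allows for women whose babies are too young to have had the MOVE visit.

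**The concern.** The birth window and the timing of the intervention do not match. The article explains that nurses thought four weeks too early and chose three or four months as the better time. The survey nevertheless includes every mother of a younger baby. In the intervention arm it therefore mixes women who have had the distinctive MOVE contact with women who have not yet been due for it.

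The mandatory four-week screen is the common background in both arms, and about 7/8 of the window has passed it. What younger-baby mothers lack is the added contact that separates the arms. If that contact carries much of the effect, the survey difference shrinks toward zero, and a small or null difference would be hard to interpret in a trial meant to inform screening policy.

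**Working it through.** **The plan's own figure.** The article mails 5000 per arm to detect a 15% rise in disclosure, read here as 15 percentage points. Abused respondents per arm run from 5000 × 0.55 × 0.08 = 220 to 5000 × 0.65 × 0.10 = 325. With 4 teams per arm and ICC 0.02, the design effect is 1 + (55 − 1) × 0.02 = 2.08 to 1 + (81.25 − 1) × 0.02 = 2.60, giving an effective size of 106 to 125. The article gives no control rate, significance level or power, so 5000 cannot be reproduced. For 80% power at two-sided 5% (normal approximation), the mailing needed is 3,015–4,455 per arm at an assumed 10% control disclosure and 4,619–6,823 at 15%. So 5000 is compatible with a control rate near 10–15%. The timing point does not depend on this.

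**Share not yet at the MOVE visit.** Assume even births and equal team sizes. With lag L months between the close of the birth window and completion, the share is (visit age − L)/8.

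| Lag | 3-month teams | 4-month teams | Mean |
|---|---|---|---|
| 0 | 3/8 = 37.5% | 4/8 = 50.0% | 43.75% |
| 1 month | 2/8 = 25.0% | 3/8 = 37.5% | 31.25% |
| 2 months | 1/8 = 12.5% | 2/8 = 25.0% | 18.75% |

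Screening later than the planned visit, which the Checklists section allows for, would raise these shares.

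**Effect on a 15-point difference, if that is the effect in women who reach the visit.**

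- No effect before the visit, no lag: 15 × 0.5625 = 8.4 points.
- Half the effect before the visit, no lag: 15 × (0.5625 + 0.5 × 0.4375) = 11.7 points.
- No effect before the visit, 1-month lag: 15 × 0.6875 = 10.3 points; 2-month lag: 15 × 0.8125 = 12.2 points.

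**Power.** Base rates are assumptions, because the article gives none. Other inputs are 4 teams per arm, ICC 0.02, 60% response, 9% abused and two-sided 5%. SE = √{[p0(1 − p0) + p1(1 − p1)]/n × DEFF}, with power from the noncentral t on 6 df.

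- Asked: n = 5000 × 0.60 = 3000, m = 750, DEFF = 1 + 749 × 0.02 = 15.98.
- Disclosure: n = 3000 × 0.09 = 270, m = 67.5, DEFF = 1 + 66.5 × 0.02 = 2.33.
- Example, asked at 50%: SE = √(0.4775/3000 × 15.98) = 0.0504, and 0.15/0.0504 = 2.97, so power is 70%. At 8.4 points the ratio is 1.65 and power is 28%.

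| Outcome, base rate | 15 points | 8.4 points (worst case) | 11.7 points (half effect) |
|---|---|---|---|
| Asked, 30% | 72% | 31% | 52% |
| Asked, 50% | 70% | 28% | 49% |
| Asked, 70% | 84% | 35% | 61% |
| Disclosure, 10% | 72% | 35% | 54% |
| Disclosure, 20% | 58% | 25% | 41% |
| Disclosure, 30% | 52% | 21% | 35% |

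**Restricting to babies of at least 4 months** keeps half the respondents (1500 for asked, 135 for disclosure) with the full 15 points. Power is then 67–82% for asked and 39–58% for disclosure over the same base rates.

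**The case against.** The strongest reply is that MOVE is more than the checklist visit. The guidelines and clinical pathway, nurse mentors and family violence liaison workers are not tied to a 3- or 4-month contact and can change what nurses do earlier. That stands: mothers of younger babies are not wholly unexposed, and 8.4 points is a worst case.

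Four further points also stand.

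- The four-week screen covers intervention-arm mothers too, so a reader should not infer that only the comparison arm had been screened by mailing.
- The 15% is not defined as an effect among women who reached the visit. The sample size section presents it as an average from an earlier study of screening against usual care. Scaling it by 0.5625 is one reading.
- The survey section plans two rounds of reminder cards, so some women will answer when their babies are older. The article states no lag, so 44% is the zero-lag figure.
- Routine data at four and twelve months fix the infant's age by design, so a conclusion of no benefit would not rest on the survey alone.

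The routine data cover the gap only in part. They come from unblinded nurses, the Checklists section says they are not recorded at the three-month point used by two teams, and they hold no Composite Abuse Scale score. Disclosure among women so classified can come only from the survey.

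One might also infer that intervention nurses postpone asking from four weeks to the later visit, which could reverse the difference in mothers of young babies. The article does not say that they do.

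**Conclusion.** The mismatch is real and follows directly from the article's own birth window and visit times. Up to about 44% of surveyed intervention-arm women have not reached the MOVE visit, given even births, equal team sizes and no lag.

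The size of the consequence is much less certain. Attenuation of the survey-based primary outcomes is probable, but the document does not fix its amount. Under the assumed base rates, power for being asked falls from 70–84% to 28–35% in the worst case, or to 49–61% if half the effect reaches younger-baby mothers. For disclosure it falls from 52–72% to 21–35%, or to 35–54%.

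A reader might conclude that the trial's primary effects are all diluted by nearly half. The documents do not support that. It would need zero effect before the visit and zero lag, and it would ignore the routine-data comparisons. That most undiluted power figures are already below 80% reflects the cluster count and the assumed base rates, not the birth window.

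**What to change.** **Before mailing.** Keep an 8-month birth cohort but move the filter to births in implementation months 1 to 8. At the end of month 12 the babies are then 4 to 12 months old, and each 3- or 4-month visit falls due within the implementation year. With even births the number of women is about the same, so the change is to the birth-date filter given to the mailing company. The costs are longer recall of the four-week screen (up to about 11 months for the oldest babies) and a 12-month abuse window that covers less of pregnancy. Abuse in pregnancy is reported separately, which limits the second cost.

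**If the mailing list is already fixed.** Prespecify, in both arms alike, an analysis limited to women whose babies are past the 4-month visit, for example with a few weeks' margin because screening may occur later. Report it beside the all-respondent analysis. This needs the baby's age or birth date at completion. An exact 4-month cut-off discards half the sample, and a margin discards more. The restricted analysis has more power than the all-respondent one in the worst case. If half the effect arrives earlier, it gains for being asked but hardly at all for disclosure (39–58% against 35–54%), which is why both should be shown.

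### The 15% behind the sample size is attached to two different outcomes and comes from a contrast the trial no longer makes, so the unqualified power claims should be restated

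*Protocol article*

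**What the plan says.** Four places in the protocol article bear on this.

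- **Survey sample size calculation.** The figure is tied to disclosure: "This sample size enables us to detect a predicted increase of 15% average disclosure found previously in a screening intervention". The source is described there as a comparison of screening with usual care. The stated inputs are 5000 questionnaires mailed per arm, a 55-65% response, an ICC of 0.02, and the expectation that "around 8-10% of women attending each of the eight MCH services will have been abused in the previous 12 months".
- **The primary outcomes for the study are to.** The figure is tied to inquiry: "Increase the proportion of women (15%) reporting that they have been asked about family violence". Disclosure is the next item and carries no figure: "Increase the proportion of women disclosing IPV (discussing IPV with MCH nurse) or nurses reporting discussing safety plans". Referral is the third.
- **MOSAIC.** After four-week screening became mandatory, "the trial design was modified to evaluate an enhanced model of IPV screening", with basic mandatory screening as the comparator.
- **Women's survey questionnaire.** "This sample gives us power to detect differences in the primary outcome", in the singular, although three primary outcomes are listed.

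Under the heading For MOVE primary outcomes, disclosure is to be reported among women who score at or above 3 and at or above 7 on the Composite Abuse Scale.

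**The concern.** The two outcomes that share the 15% are not interchangeable. One is a proportion of all respondents. The other is a proportion of the roughly one in ten who have been abused, with a different sample, design effect and base rate. A statement of detectable effect for one says little about the other.

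The planning effect was also not revisited when the comparator changed. A difference seen between screening and usual care is not evidence of what to expect when both arms are required to screen.

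At stake is what the trial can say about disclosure, a primary outcome and the one the sample size section names. A reader who takes the power statement at face value may give a null disclosure result more weight than it can bear.

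**Working it through.** **Inputs from the article.** 5000 mailed per arm; response 55-65%; abuse prevalence 8-10%; ICC 0.02; eight teams, four of them intervention teams, so k = 4 per arm.

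**Assumptions, because the article is silent.** Two-sided alpha 0.05; 80% power as benchmark; equal team sizes; 15% read as an absolute difference; the 8-10% prevalence applied to respondents as the disclosure denominator.

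**1. The plan's own figure.** It cannot be reproduced uniquely without a base rate, alpha or power. Working backwards with the usual formula, 80% power for +15 points in disclosure needs this many mailed per arm (the range spans the response and prevalence ranges):

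- base 10%: 3015-4455
- base 15%: 4619-6823
- base 20%: 6712-9915

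So 5000 per arm fits a comparison-arm disclosure rate somewhat above 10%, which the article never states.

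**2. Sample and effective sample per arm.** Design effect DE = 1 + (m - 1) × 0.02, with m = n/4; effective n = n/DE.

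| Denominator | n | m | DE | Effective n |
|---|---|---|---|---|
| Abused, low: 5000 × 0.55 × 0.08 | 220 | 55 | 2.08 | 106 |
| Abused, high: 5000 × 0.65 × 0.10 | 325 | 81.25 | 2.605 | 125 |
| All, low: 5000 × 0.55 | 2750 | 687.5 | 14.73 | 187 |
| All, high: 5000 × 0.65 | 3250 | 812.5 | 17.23 | 189 |

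With four teams per arm, effective n cannot exceed 4/0.02 = 200 however many questionnaires are mailed.

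**3. Power for +15 points in disclosure among abused women.** Usual formula: Φ[(0.15 - 1.96 × SE0)/SE1], with SE0 from the pooled proportion and SE1 from the separate proportions. The t(6) version uses a noncentral t with 8 - 2 = 6 df and noncentrality 0.15/SE1.

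Example, 20% to 35% with effective n 106:
- SE0 = √(2 × 0.275 × 0.725/106) = 0.0613
- SE1 = √((0.20 × 0.80 + 0.35 × 0.65)/106) = 0.0605
- usual power = Φ[(0.15 - 0.1202)/0.0605] = Φ(0.49) = 69%
- on t(6), noncentrality 2.48 against a critical value of 2.447 gives 55%

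| Comparison-arm disclosure | Usual formula | t(6) |
|---|---|---|
| 5% | 92-95% | 80-86% |
| 10% | 82-88% | 69-76% |
| 20% | 69-76% | 55-62% |
| 30% | 62-69% | 48-55% |
| 40% | 59-66% | 46-52% |
| 50% | 60-67% | 47-53% |

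Using unpooled variance throughout moves the middle column up by about one point (60-77% over base rates of 20-50%).

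Power is at least 80% up to a base rate of about 11-16% (usual) or 5-8% (t(6)), and again from about 69-74% (usual) or 77-80% (t(6)) upwards.

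**4. Power for +15 points in being asked, all respondents.** The usual formula gives at least 83% at every base rate. On t(6) power is below 80% for base rates of about 18-67%, with a minimum of about 69% near 40%.

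**5. Detectable difference at 80% power.**

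| Outcome and base rate | Usual formula | t(6) |
|---|---|---|
| Disclosure, 10% | 13-14 points | 16-18 points |
| Disclosure, 20% | 16-17 points | 19-21 points |
| Disclosure, 30% | 17-19 points | 20-22 points |

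**6. Which denominator the disclosure figure can mean.** A 15-point absolute rise in disclosure among all women would exceed the 8-10% expected to have been abused. On an absolute reading, the figure makes sense only among abused women.

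**The case against.** A reader might infer that the design lacks the power it claims. The documents do not support that. No base rate is given, and the nearest hint points to low disclosure: the MOSAIC section reports that nurses in the earlier trial had difficulty identifying abused clients. At 10% the usual formula gives 82-88% for +15 points, so the sample size statement could be true as written. For being asked it gives at least 83% throughout. Mandatory, prompted and reported screening also makes a high comparison-arm asking rate possible, where even t(6) power recovers.

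The 6 df are my choice. The article says only that clustering was allowed for, and it plans robust standard errors without naming a small-sample reference distribution. I think t(6) is sound with eight teams, but it is not a stated input, so both sets of figures are shown.

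Alpha, power and base rate are details that an article may leave to the full protocol, so their absence is not the fault. Nor is the origin of the 15% hidden: the sample size section names its source and the redesign is openly described. That a null result would be misread is a risk, not something the text shows.

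What survives is that the article ties one figure to two outcomes, keeps an effect from the replaced contrast without re-justifying it, and claims power without qualification for a single primary outcome when it lists three. Condensation does not explain these, because they are statements the article makes.

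**Conclusion.** The sample-size claim is inconsistent and outdated as written. The 15% belongs to being asked in one section and to disclosure in another, on denominators of about 2750-3250 and 220-325 per arm, and it was taken from screening versus usual care.

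Whether the claim of power holds depends on a disclosure rate the article does not state. Under the listed assumptions, a 15-point difference in disclosure reaches 80% power only at a low comparison-arm rate or a very high one. Between 20% and 50%, power is about 60-77% by the usual formula (unpooled variance; 59-76% pooled) and 46-62% on t(6). For being asked, any shortfall appears only on t(6).

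This is a fault in how the claim is stated. It does not show that the number of questionnaires is wrong, and mailing more would help little for being asked, where effective n is already 187-189 against a ceiling of 200.

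**What to change.** In the list of primary outcomes and the sample size section, say which outcome the 15% refers to, in which denominator, and whether it is absolute. State that it was derived from screening versus usual care and is not the expected effect of enhanced over basic mandatory screening.

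In the sample size and women's survey questionnaire sections, replace the unqualified power statements with the detectable difference for each survey primary outcome, given four teams per arm, ICC 0.02 and a stated range of base rates. Name the reference distribution used.

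The cost is a few lines of text and a less favourable detectable difference. The teams, the mailing and the analysis do not change.
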